### Study endpoints

Primary:

The primary endpoint of this study is the PRNT
_50_ titres post booster vaccination according to intervals between primary Yellow Fever vaccination and the booster dose.

Secondary:

The secondary endpoint is the rate of YF PRNT seroreversion (seropositive to seronegative) over a period of 9 months to 8 years following a single primary dose of YF vaccine administered to Gambian infants at nine months age.

Exploratory (Sub-study only):

Frequency of activated T cells, following re-stimulation with YF, in children of different ages following a booster dose of YF vaccinationLevels of YF specific memory B cells in children of different ages following a booster dose of YF vaccinationPossible impact of early innate responses, as measured by RNASeq, on antibody, B and T cell responses

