### Study design

This is a Phase 3 clinical trial to establish safety and immunogenicity of a booster dose of licensed YF vaccine in children of different age groups, following primary immunization with the same vaccine at 9–10 months of age.

The proposed study leverages three well-characterized cohorts of infants, all of whom were vaccinated with the Institut Pasteur de Dakar 17D YF vaccine at 9–10 months of age within clinical trials run by the Vaccines & Immunity Theme in the MRC Unit The Gambia at the London School of Hygiene and Tropical Medicine (MRCG) over the last few years (
Figure 1). The databases of the previous trials, the YF PRNT
_50_ results from the primary immunisation and the stored samples are immediately available to the investigators. Consent for sample storage and future work on remaining samples was obtained at the time of initial recruitment.

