### Statistical considerations

**
*Sample size considerations*
**

The primary endpoint of this study is the PRNT titres post booster vaccination according to intervals between primary YF vaccination and the booster dose. A sample size of 250 participants per cohort provides a precision of around +/- 5% over a range of plausible seroconversion rates associated with boosting at the three different timepoints (
Table 3).

**Table 3. T3:** Precision around given estimates of seroconversion based on a sample size of 250 participants per group.

Seroconversion	95% confidence interval
95%	91.6 – 97.1
90%	85.7 – 93.1
80%	74.6 – 84.5
70%	64.1 – 75.3
60%	53.8 – 65.9
50%	43.9 – 56.2

The same sample size also provides over 80% power to detect a 10% difference in the seroconversion/seroreversion rates between two cohorts assuming a rate of at least 85% in one cohort, and over 90% power to detect a 15% difference in any two seroconversion/seroreversion rates.

Exploratory immunology sub-studies:

Our previous systems biology studies showed that significant differences in “omic” signatures over the first week of life and according to day of life were detectable in cohorts of infants as small as n=10 per group. We cannot currently confirm if such “omic” changes are informative to predict responses to YF vaccine in young children, but based on the data from Querec
*et al.*, systems biology approaches were informative in adults in group sizes as small as n=15
^
25
^. We are therefore confident that a group size of 30 per sub-group will provide us with sufficient datasets to not only explore if “omic” signatures in children are also predictive of humoral responses to the booster, but also to interrogate pathways and cellular populations involved in mediating correlates of protection against yellow fever.

**
*Data presentation and analysis*
**

Baseline data:

All baseline data including demographic and anthropological parameters will be tabulated by age cohort along with appropriate measures of spread. 

Immunogenicity data:

Descriptive evaluations including yellow fever PRNT GMT, seropositivity, seroreversion rates between 9 months and boost and seroconversion rates following boost (including the number of participants who seroconvert or who have a four-fold rise in antibodies concentrations) and relevant differences in these measures between age cohorts will be calculated and presented with appropriate measures of spread.

GMT data will be log

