### Ethical considerations

This study is conducted in accordance with the principles set forth in the ICH Harmonised Tripartite Guideline for Good Clinical Practice
^
26
^ and the Declaration of Helsinki in its current version
^
27
^, whichever affords the greater protection to the participants. The protocol was approved by the Gambia Government/MRC Joint Ethics Committee and the LSHTM Research Ethics Committee.

**
*General considerations on human subject protection*
**

The study staff will ensure that the participants’ anonymity is maintained. The participants will be identified only by a participant’s ID number on the CRF and any electronic database. All documents will be stored securely and only accessible by study staff and authorised personnel. The study will comply with the Data Protection Act, which requires data to be anonymised as soon as it is practical to do so.

**
*Rationale for participant selection*
**

The investigators aim to enrol children who have received a documented initial YF vaccine (in between the age of 9–11 months) while participating in previous trials conducted in The Gambia. Conducting this trial among children who had been participants in previous trials will enable the study to calculate more accurately the immunogenicity effect of a booster YF vaccine and assess the effect of time interval in between the first dose and the booster on the immunogenicity. On the other hand, there are additional data which were collected from these children during their participation in previous trials (such as anthropometric data), which will permit a better assessment of the immunogenicity of a booster dose, taking into account possible confounding factors. Finally, The Gambia is an endemic setting of YF, and shares many similarities with other endemic settings, which will facilitate future generalisability of the findings to the target population and drive a potential vaccine policy change in these settings.

**
*Evaluation of risks and benefits*
**

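### The between-cohort comparison of seroreversion uses the post-primary titre only as positive or negative, so a crude difference mixes strength of priming with waning

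*Protocol article*

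**What the plan says.** Study endpoints makes the secondary endpoint the "rate of YF PRNT seroreversion (seropositive to seronegative) over a period of 9 months to 8 years following a single primary dose". Statistical considerations (Immunogenicity data) lists among its descriptive evaluations "seroreversion rates between 9 months and boost and seroconversion rates following boost" and adds that "relevant differences in these measures between age cohorts will be calculated and presented with appropriate measures of spread". No covariate or stratification is named for seroreversion. The sample size text claims "over 80% power to detect a 10% difference in the seroconversion/seroreversion rates between two cohorts assuming a rate of at least 85% in one cohort"; for 15 points between any two rates, it claims more than 90%. The only between-cohort method named is a two-sample t-test on log2 titres, for GMT ratios.

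Study design says of the earlier trials that the PRNT50 "results from the primary immunisation and the stored samples are immediately available to the investigators". The Rationale section is narrower: post-primary serology is documented for most children, and serum is stored for the others. Laboratory investigations says that stored serum will be assayed where results are missing. Selection of participants allows recruits from community health centres as an exception.

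Ethical considerations says that data from the earlier trials exist, "which will permit a better assessment of the immunogenicity of a booster dose, taking into account possible confounding factors". That sentence concerns the booster response and gives no method. Full analysis detail is left to a statistical analysis plan, due before database lock and not shown.

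**The concern.** Each child contributes one interval between priming and booster, so the course from 9 months to 8 years is built from contrasts between cohorts. Whether a child crosses the cut-off depends on how far above it the child started and on how much titre was lost. A child who starts just above it reverts after a small loss, while a child who starts high can lose many-fold and not count. Restricting the denominator to post-primary seropositives removes primary non-responders but leaves differences in height above the cut-off.

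The protocol gives its own reasons why priming may differ by cohort. Table 1 dates the primary doses to 2013-14, 2018 and 2020-22, in three separate trials. The oldest cohort had inactivated polio and measles-rubella vaccines in various combinations; the two younger ones had measles-rubella, oral polio and pneumococcal vaccine. The Background says that giving the first measles vaccine together with the yellow fever vaccine interferes with yellow fever immunity. Any such difference lies along cohort, and hence along interval. At stake is how the seroreversion course is interpreted, in a trial whose main objective is whether a booster is needed and, if so, when.

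**Working it through.** **1. The plan's own power figures.** Inputs: n = 250 per cohort (Statistical considerations) and two-sided alpha 0.05 (assumed, in line with the 95% intervals). For two unadjusted proportions, power = Φ{[√n·|p1−p2| − 1.96·√(2p̄(1−p̄))] / √(p1(1−p1)+p2(1−p2))}.

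- 85% vs 75%: (1.581 − 1.109)/0.561 = 0.84, power 0.800.
- 90% vs 80%: 0.882. 95% vs 85%: 0.963.
- 15 points, least favourable pair (57.5% vs 42.5%): (2.372 − 1.386)/0.699 = 1.41, power 0.921.

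The stated figures reproduce (borderline at exactly 85% vs 75%) as those of a crude comparison of two proportions. Only post-primary seropositives can serorevert, so the denominator may be below 250: at 225 per cohort, 85% vs 75% has power 0.757.

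**2. Why starting height matters.** The documents give no post-primary mean, SD or decline by cohort, so everything from here on is assumed. Let X be the post-primary log2 titre, D the log2 decline and c the cut-off. Seroreversion is P(X − D < c | X ≥ c). Take D ~ N(3, 1.5²). A child starting 1 log2 above the cut-off reverts with probability Φ((3−1)/1.5) = 0.91; one starting 6 log2 above, with probability Φ((3−6)/1.5) = 0.02.

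**3. Identical waning, unequal priming.** Base case: X ~ N(8, 2²), the same D in both cohorts, cut-off 1:10 (c = 3.32).

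| Priming of the second cohort | Seroreversion | Difference from equal priming |
|---|---|---|
| equal | 24% | 0 |
| 1.4-fold lower (0.5 log2) | 31% | 6 points |
| 2-fold lower (1 log2) | 37% | 13 points |

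Other assumptions, 2-fold gap:

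- Post-primary mean 7 to 9, SD 1.5 to 2, decline 2 to 4 log2: 6 to 18 points.
- Reference mean 4 log2 above the cut-off, SD 1.5 to 2, decline 2 to 3 with SD 1: 11 to 20 points.
- Base case, but with decline rising by 0.4 to 0.6 log2 per log2 of starting titre: 8 down to 5 points.

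A two-fold gap is one step of the PRNT dilution series.

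**4. What adjustment does.** Simulated two-cohort trials, base case, n = 250 each; crude test of two proportions against logistic regression with post-primary log2 titre as covariate. The ranges are over repeated runs.

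| Truth | Crude rejects | Adjusted rejects |
|---|---|---|
| equal priming, equal waning | about 5% | 5-6% |
| 1.4-fold lower priming, equal waning | 32-36% | 5-6% |
| 2-fold lower priming, equal waning | 87-89% | 4-6% |
| equal priming, waning differs by 0.5 log2 | 40-41% | 58-61% |
| nothing differs, one cohort's post-primary titres read 1.4-fold low | 5% | 56-57% |
| nothing differs, one cohort's post-primary titres read 2-fold low | 7% | 98-99% |

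The last two rows are the price of adjustment: a systematic assay shift in one cohort barely touches the crude test but makes the adjusted one reject.

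**The case against.** **It belongs to the analysis plan.** Covariates for a secondary endpoint are commonly settled there, and the protocol defers full detail to it. This stands to the extent that adjustment is unspecified, not excluded. But the protocol does write down a crude comparison and gives power for it, so this is a comment on a stated method.

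**The crude rate is the endpoint.** It estimates the endpoint as defined. For the question of whether a booster is needed, the share of children who have lost seropositivity matters whatever the cause. This stands, and is why the crude rates should stay. They do not by themselves show that a difference between cohorts is one of waning.

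**The post-primary result is already used.** It sets who can serorevert, so a reader who infers that the plan ignores it altogether goes too far; only its height above the cut-off is unused. Nor is a titre on file for every child: some sera are still to be assayed, and community recruits may have none.

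**Nothing shows unequal priming.** All cohorts received the same manufacturer's vaccine at 9 to 10 months, and measles-rubella vaccine appears in all three. This stands: the protocol gives a reason to check, not evidence of a gap.

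**Adjustment can mislead.** The Rationale refers to earlier assays in Berlin; Laboratory investigations allows later testing in Dakar or Berlin. The crude endpoint needs comparable titres only at the cut-off, adjustment along the whole scale. This stands, and it limits the remedy.

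**Conclusion.** The point holds in a limited form. The stated comparison of seroreversion is an unadjusted difference between non-randomised cohorts and disregards how far above the cut-off each child started. It cannot separate weaker priming from faster waning. With identical waning, a two-fold priming gap would show as roughly 5 to 20 points, depending on the assumed titre spread, mean decline and whether decline rises with starting titre. None of these inputs is in the documents.

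A reader might infer that the seroreversion course is biased in a known direction, or that the plan commits itself to reading cohort differences as waning. The documents support neither: they show no priming gap, and they call these evaluations descriptive. A reader might also infer that the adjusted comparison should replace the crude one. The assay-shift result argues against that; the two belong side by side. This is an inexpensive improvement worth making.

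**What to change.** In the statistical analysis plan, before database lock:

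- Keep crude seroreversion per cohort, with its interval, as the description of the endpoint. State that the denominator is children seropositive after the primary dose.
- Add a between-cohort comparison with post-primary log2 PRNT50 as covariate (for example logistic regression), or seroreversion standardised to the pooled post-primary distribution.
- Show post-primary titre distributions by cohort and the within-child log2 decline from post-primary to pre-booster.
- Attribute a cohort difference to waning only if the crude and adjusted results agree.
- Report by cohort which laboratory and assay period produced the post-primary titres, and give a sensitivity analysis for a systematic shift in one cohort.
- Report how many children have no post-primary titre; they are outside both analyses.

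The cost is a paragraph of wording, one extra model and the sensitivity analysis; no new samples are needed beyond the stored sera already due for assay. The downside is reliance on a model and on titres that are comparable along the whole scale. If the database is already locked, the added comparison should be labelled post hoc.

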### Planned interim analyses

Safety endpoints will be reviewed by the DSMB at timepoints specified in the DSMB charter. No additional interim analyses are planned. No interim analyses of immunogenicity data are planned.

### Statistical Analysis Plan

Full details of the final statistical analysis to be undertaken in the trial will be set out in the statistical analysis plan (SAP). A full SAP detailing all the analysis and management of missing data is not available yet. This will be provided before database lock. In case of amendments or decision to deviate from the SAP, updated versions of the SAP will be communicated as well to the MCA.

### Data handling and record keeping

**
*Data Management and Processing*
**

Full details regarding the handling of trial data will be described in the trial data management plan (DMP) which will be consistent with appropriate data management SOPs of the Unit and applicable regulatory requirements. All documents used during the trial will be version controlled and dated.

Source will be defined for all data to be collected during the trial in a source data designation log. Electronic CRF (eCRF) will act as the source for certain data. Other data will be transcribed from alternative source documents. These might include the infant welfare card held by the mother, clinical notes, reactogenicity record forms and the vital signs and anthropometry card. Certified photocopies of relevant source documents will be made for subsequent source data verification (SDV) purposes when appropriate.

Subject data will be collected or transcribed contemporaneously into the eCRF according to written CRF completion guidelines for the trial. The eCRF will be developed with the input of sponsor, investigator and data management personnel. Draft eCRFs will be piloted by the investigator site and will be reviewed to ensure all protocol required data for the assessment of the trial endpoints are collected and also that the data required to confirm protocol compliance are captured.

Data entered into the eCRF will include screening number, initial immunization date with YF vaccine, information on the visit number, the date of the visit and, when relevant, the time that particular activities were undertaken (e.g. to confirm the time interval between vaccination and the recording of the post-vaccination vital signs). The individual member of the clinical trial team entering data into the eCRF will be captured as part of the entry process using a unique identifier. Such information will allow the designation of clinical trial staff completing the eCRF to be confirmed within the database.

**
*Data security*
**

During this study, we will be abiding to the General Data Protection Regulation and to our data protection policy, which mandates that all staff using personal data must ensure that they hold such data securely and that it is not disclosed to any unauthorised third party in any way, including by accident. Data breaches will be reported to the data protection officer immediately, to the IEC, and to the MCA. Investigations will be made to identify the root cause of the breach and addressed appropriately.

**
*Source documents and access to source data*
**

A subject folder will be maintained for all children and will contain the consent documentation, and the source documents including the clinical notes written on all participants in the trial.

The Principal Investigators will maintain appropriate medical and research records for this study in compliance with the principles of good clinical practice and regulatory and institutional requirements for the protection of confidentiality of participants. The study team members will have access to records.

The authorised representatives of the sponsor, the ethics committee(s) or regulatory bodies may inspect all documents and records required to be maintained by the investigator, including but not limited to, medical records (office, clinic, or hospital) for the participants in this study. The clinical study site will permit access to such records.

**
*Protocol Deviations*
**

A protocol deviation (PD) is any noncompliance with the clinical trial protocol, good clinical practice (GCP), or other applicable regulatory requirements. The noncompliance may be either on the part of the participant or the investigator, including the study team members, and may result in significant added risk to the study participant. As a result of a deviation, corrective actions will be developed and implemented promptly.

If a deviation from, or a change of, the protocol is implemented to eliminate an immediate hazard(s) to the trial participant without prior ethics approval, the PI or designee will submit the implemented deviation or change, the reasons for it, and, if appropriate, the proposed protocol amendment(s) as soon as possible to the sponsor for agreement and the relevant independent ethics committee (IEC) and MCA for review and approval before implementation.

The PI or designee will document and explain any deviation from the approved protocol on the CRF, where appropriate, and record and explain any deviation in a protocol deviation form that will be maintained as an essential document. All protocol deviation will be reported to IEC and to the MCA.

### Study monitoring

Study monitoring will be undertaken to verify that the rights and well-being of the children enrolled in the trial are protected, that the data reported are accurate, complete and verifiable from source documents and that the trial is conducted in compliance with the current trial protocol, with ICH-GCP guidelines, and with applicable regulatory requirements.

Full details of the monitoring to be undertaken prior to, during, and at the end of the trial will be documented in the trial monitoring plan which will be agreed and signed off by the sponsor prior to trial initiation. Monitoring will include a site initiation visit which will be undertaken prior to the first subject consent, on-site monitoring visits throughout the trial and a close-out visit. Remote monitoring of the trial database may also be undertaken.

### Ethical considerations

This study is conducted in accordance with the principles set forth in the ICH Harmonised Tripartite Guideline for Good Clinical Practice
^
26
^ and the Declaration of Helsinki in its current version
^
27
^, whichever affords the greater protection to the participants. The protocol was approved by the Gambia Government/MRC Joint Ethics Committee and the LSHTM Research Ethics Committee.

**
*General considerations on human subject protection*
**

The study staff will ensure that the participants’ anonymity is maintained. The participants will be identified only by a participant’s ID number on the CRF and any electronic database. All documents will be stored securely and only accessible by study staff and authorised personnel. The study will comply with the Data Protection Act, which requires data to be anonymised as soon as it is practical to do so.

**
*Rationale for participant selection*
**

The investigators aim to enrol children who have received a documented initial YF vaccine (in between the age of 9–11 months) while participating in previous trials conducted in The Gambia. Conducting this trial among children who had been participants in previous trials will enable the study to calculate more accurately the immunogenicity effect of a booster YF vaccine and assess the effect of time interval in between the first dose and the booster on the immunogenicity. On the other hand, there are additional data which were collected from these children during their participation in previous trials (such as anthropometric data), which will permit a better assessment of the immunogenicity of a booster dose, taking into account possible confounding factors. Finally, The Gambia is an endemic setting of YF, and shares many similarities with other endemic settings, which will facilitate future generalisability of the findings to the target population and drive a potential vaccine policy change in these settings.

**
*Evaluation of risks and benefits*
**

The risks to either infants, pre-school children or school age children taking part to this study are low, as the YF vaccines used in this trial are licensed, have proven to be safe, and these children have initially received a YF vaccine in previous trials and via routine EPI programs worldwide without raising major safety concerns. Also, the vaccines are currently used in the routine EPI schedule in The Gambia and as such trial participation per se is not associated with any increase in risk with this regard.

Nonetheless, the administration of any vaccine can be associated with local and systemic adverse reactions which can be severe or, exceptionally rarely, even life-threatening. The safety of participants will be monitored closely for 30 minutes following vaccination as standard practice by the investigator, local safety monitor and sponsor.

Blood sampling can cause some pain at the time and occasionally results in the development of a bruise but has no other risks. The volumes of blood to be taken, even in infants, are not of physiological significance.

Receiving a booster vaccine for Yellow Fever could be of significant benefit for these children living in an endemic setting for the disease and who, outside of this trial, are unlikely to receive this booster.

**
*Informed consent*
**

For those expressing an interest for their children’s participation, informed consent will not be undertaken on the same day as individual sensitization to ensure all caregivers have the chance to consider the information overnight, at least, prior to providing consent.

Written/thumb-printed informed consent will only be required from one caregiver, but in all cases, it will be confirmed that other caregivers are aware of the study and are supportive.

For children who are 6 years of age and above, oral assent will be obtained from them in addition to their caregiver’s written/thumb-printed consent. This oral assent will be documented in the clinical notes.

Information regarding the trial will initially be given to caregivers by a field worker or nurse, although all caregivers will also be given the chance to ask a study clinician any questions they may have regarding the trial prior to the assessment of understanding and consent documentation.

Given the low rate of English literacy and the vulnerability of the groups (children), the process of obtaining informed consent is of exceptional importance and will be a focus for trial monitoring activities. No remuneration for enrolling in the trial will be provided. Transport fares will be provided. All information required by ICH-GCP will be provided to potential mothers through the ICD. All ICD in use will be approved by the Gambia Government/MRCG Joint Ethics Committee. Should any new information which is considered to have potential implications for informed consent become available during the trial this will be made available to study participants and informed consent will be repeated using a further approved ICD. The provision of informed consent is an ongoing process and can be withdrawn at any time.

**
*Participant confidentiality*
**

All participant-identifiable information (names, addresses, contact details etc) will be held securely and will not be available to anybody other than those in the investigator team, external monitors or auditors working on behalf of the sponsor and, on request, and rightful individuals from the Gambia Government/MRCG Joint Ethics Committee and the National Regulatory Authority (The Medicines Board). Information on this will be included as part of the informed consent process. Paper records including identifiable source documents will be held securely in access-restricted filing cabinets. Electronic records will be on access-restricted servers in line with the applicable data security and data access policies.

**
*Future use of stored specimens*
**

Additional consent will be obtained for the storage and future use of any specimens remaining following the assessment of the specified endpoints for research of relevance to the people of The Gambia and related to vaccination, immunity and infection. Such additional consent is not required for enrolment in the main trial but will be obtained at the same time as consent to the overall trial. Following use of collected specimens for the primary, secondary and exploratory endpoints, the future use of any remaining stored specimens would require the approval of the Gambia Government/MRCG Joint Ethics committee.

